**Methods:**

The study is a multicenter, randomized, two-arm crossover noninferiority trial of pediatric hemato-oncology patients that will be conducted within the usual clinical workflow. Patients’ LP procedures will be performed alternately either with the IQ-Tip system (study arm A) or a conventional Quincke-type 22G spinal needle (study arm B). For each enrolled patient, the order of procedures is randomly assigned either as ABAB or BABA. The total number of LP procedures will be at least 300, and the number of procedures per patient between two and four. After each study LP procedure, the performance will be recorded immediately, and 1-week diary-based and 4-week record-based follow-ups on symptoms, complications, and adverse events will be conducted thereafter. The main outcomes are the incidence of traumatic LP, first puncture success rate, and incidence of post-dural puncture headache.

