### Data analysis

Mean, standard deviation (SD), median, interquartile range (IQR), range, and proportions will be used as the main descriptive statistics as appropriate for the data. A cumulative distribution curve will be used as the main descriptive statistics for erythrocyte count data in CSF [14]. This curve illustrates the respective proportions of CSF samples, which denote the incidence of TLP for any given criterion of the erythrocyte count. For the chosen criterion, the incidence of TLP is the vertical distance (in %) from the corresponding curve point up to the 100% point.

The sample size was estimated by an online power calculator for a binary outcome in a non-inferiority trial [31]. For the estimation, it was assumed that the incidence of TLP with the IQ-Tip needle system (study arm A) is 20% and 30% with the conventional spinal needle (study arm B). The values are based on our data on the IQ-Tip system [19] and conventional needle [14] in pediatric hemato-oncology patients, respectively. Considering the 5% noninferiority margin, about 150 LP procedures in both arms will be needed to achieve 90% statistical power to demonstrate noninferiority at the significance level of *p* < 0.05. Assuming a total of 26 TLPs out of 150 procedures in the arm A, corresponding to the 17.3% incidence of TLP in our previous study [19], the total number of TLPs in the arm B should be at least 30 (20%) to demonstrate noninferiority, and at least 40 (26.7%) to demonstrate superiority for the IQ-Tip system. These relationships are illustrated in Fig. 2.

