Incidence of symptoms, complications, and adverse events	Search from hospital electronic health records	Occurrence (yes/no)	Proportion	Within four weeks after each study LP procedure

As an exploratory analysis, logistic regression analysis will be performed to assess factors that may account for the incidence of TLP, defined as a dichotomous variable (yes/no) by the criterion of ≥ 10 erythrocytes/μL. The TLP values will be obtained from the patients’ 2nd, 3rd, and 4th study LP procedures. The following dichotomous variables (yes/no) will be entered to the model as predictors: whether the preceding procedure was performed with a conventional spinal needle, whether the preceding procedure was TLP, whether the consecutive procedures were performed within a week (≤ 7 days) or two (≤ 14 days), whether the patient was obese (BMI ≥ 30 kg/m^2^), whether the provider was experienced with more than 100 previous LP procedures, and whether the thrombocyte count was less than 50,000 platelets/μL [11, 12, 14, 19]. Estimated odds ratios (OR) of the entered predictors will be reported with 95% CIs. The robustness of predictors and related ORs will be verified by performing both backward and forward regression analyses.

Statistical analyses will be done with a concurrent version of IBM SPSS Statistics for Windows (IBM Corp., Armonk, NY, USA).

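### Forward and backward selection on the same 38 to 56 or so events cannot verify the exploratory TLP model, and odds ratios kept for significance tend to be too large

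*Protocol article*

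**What the plan says.** The model is described after Table 2 in the Data analysis section of the protocol article, and is labelled exploratory there. The outcome is TLP yes/no at 10 or more erythrocytes per microlitre. The first study LP of each patient supplies no outcome: "The TLP values will be obtained from the patients’ 2nd, 3rd, and 4th study LP procedures".

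The predictors form a fixed list of dichotomous variables: the needle used at the preceding LP, a preceding TLP, the interval since the preceding LP, obesity, provider experience and a low platelet count. The interval is worded with two cut-offs: "whether the preceding procedure was TLP, whether the consecutive procedures were performed within a week", followed by a 14-day alternative. The text does not settle whether one or two interval terms are meant.

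The section then commits to odds ratios with 95% confidence intervals for the predictors entered, and closes: "The robustness of predictors and related ORs will be verified by performing both backward and forward regression analyses". It gives no entry or removal threshold. It names only logistic regression, with no provision for repeated LPs in a patient.

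On size, the abstract states: "The total number of LP procedures will be at least 300, and the number of procedures per patient between two and four".

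**The concern.** A robustness check should be able to fail when the result is fragile and pass when it is not. Forward and backward selection work through the same rows, candidates and outcomes. If a predictor stands out by chance in this sample, both routines will tend to keep it. Their agreement says how the search behaves in one dataset. It says nothing about whether the predictor would reappear in another, or whether its odds ratio is near the truth. Because the sentence covers the odds ratios as well as the predictors, a selected-model estimate could be offered as confirmation of the size of an effect.

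At stake is how the trial reports on platelets, provider experience, obesity, timing and a previous TLP. Readers may give a predictor described as verified more weight than a few dozen events can bear.

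A second, smaller matter concerns the standard errors. A patient can contribute up to three rows (LPs 2, 3 and 4), and ordinary logistic regression treats them as separate patients.

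**Working it through.** **Step 1. The plan's own figure.** The article gives no event count for this model, so the planning rates must supply it: "it was assumed that the incidence of TLP with the IQ-Tip needle system (study arm A) is 20% and 30% with the conventional spinal needle". The related statement is "Considering the 5% noninferiority margin, about 150 LP procedures in both arms will be needed to achieve 90% statistical power". With variance 0.20×0.80 + 0.30×0.70 = 0.37 and distance to the margin 0.10 + 0.05 = 0.15:

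- power at 150 per arm, one-sided 0.05: Φ(0.15/√(0.37/150) − 1.645) = 91.5%
- number needed for 90%: (1.645 + 1.282)² × 0.37/0.15² = 141 per arm

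The stated figure of about 150 is therefore consistent with these rates at a one-sided 0.05 level, and their mean of 25% is a fair basis for the event count.

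**Step 2. Rows and events.** Dropping each patient's first LP leaves rows = 300 − 300/k, where k is the number of LPs per patient. Events = rows × TLP rate. Besides the 25% mean, the section's worked counts imply pooled rates of (26 + 30)/300 = 18.7% and (26 + 40)/300 = 22.0%.

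| LPs per patient | Patients | Rows | Events at 18.7% | at 22.0% | at 25% |
|---|---|---|---|---|---|
| 2 | 150 | 150 | 28 | 33 | 37.5 |
| 3 | 100 | 200 | 37 | 44 | 50 |
| 4 | 75 | 225 | 42 | 49.5 | 56.25 |

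At 25% this gives 5.4 to 8.0 events per predictor with seven terms, or 6.2 to 9.4 with six.

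**Step 3. What a significance criterion does to a retained odds ratio.** In simulated full models with seven binary predictors (assumed prevalences, 25% TLP), the median standard error of the log odds ratio for a preceding TLP was 0.45 with 150 rows and 0.36 with 225. A positive term is kept only if its log odds ratio exceeds z × SE. For a true odds ratio of 2.0 (log 0.693), the chance of being kept is P = 1 − Φ((z·SE − 0.693)/SE). The median when kept is exp(0.693 + SE × Φ⁻¹(1 − P/2)).

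| Rows | Criterion | Smallest odds ratio kept | P(kept) | Median when kept, formula | Simulated selection |
|---|---|---|---|---|---|
| 150 | p<0.10 | exp(1.645×0.45) = 2.10 | 46% | 2.79 | 2.80 (backward) |
| 150 | p<0.05 | exp(1.96×0.45) = 2.42 | 34% | 3.08 | 3.05 (forward) |
| 225 | p<0.10 | exp(1.645×0.36) = 1.81 | 61% | 2.40 | 2.38 (backward) |
| 225 | p<0.05 | exp(1.96×0.36) = 2.03 | 49% | 2.57 | 2.53 (forward) |

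The formula contains no stepwise search, only the threshold, and it reproduces the selected-model medians. In the full model without a filter, the median for the same predictor was 2.14 (150 rows) and 1.99 (225 rows).

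**Step 4. Is it the search or the filter?** Further simulations had one true odds ratio of 2 and six null predictors. The same p<0.10 rule was applied to backward selection and to the unselected full model.

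- Median odds ratio of the true predictor when flagged: full model 2.81, backward 2.68 (150 rows); 2.41 and 2.34 (225 rows). A separate set of runs gave 2.92 and 2.82, then 2.44 and 2.39.
- At least one null predictor flagged: about 46% in the full model, 44 to 47% with backward selection. Six independent tests at 0.10 would give 1 − 0.9⁶ = 47%.
- Without any filter, the full model's 95% interval covered the truth in 95% of datasets.

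**Step 5. Does agreement mean anything?** With backward removal at 0.10 and forward entry at 0.05, the two routines chose the same set in about 51% of datasets. With no true effects, backward kept at least one predictor in about 47% and forward in about 23 to 25%.

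**Step 6. Repeated LPs.** For a predictor that is constant within a patient, such as obesity, three equally correlated rows multiply the variance by about 1 + 2ρ relative to independence. The article gives no within-patient correlation ρ, so this effect cannot be sized. For a predictor that alternates within a patient, the ordinary standard error may instead be too large.

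**The case against.** The strongest reply is that the article already does the main thing right. The predictors are fixed in advance, and the odds ratios promised are those of the predictors entered, which on a plain reading is the full model. Selection comes afterwards as a check. The analysis is exploratory and does not touch the noninferiority conclusion. Thresholds, coding and clustering may be settled in an analysis plan that is not shown. The check is also not empty, since the two routines can disagree and often do.

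Most of this stands. What remains is the verification sentence, which the article itself fixes and which assigns to selection a task it cannot perform.

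A reader might go further and infer four things that the documents do not support:

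- *The reported odds ratios will be overstated.* Full-model estimates were close to the truth (at most about 7% high: 2.14 against 2.0). The overstatement belongs to estimates retained for significance.
- *Stepwise selection itself causes the inflation.* Step 4 shows the same inflation and the same rate of null flags in the full model under the same filter.
- *The 7-day and 14-day terms bias the odds ratios because one is nested in the other.* Two terms are only one reading of the clause. If both are entered, they span the same space as a three-level interval variable, so the fit is identical. Nesting widens standard errors and makes selection between the terms unstable, without biasing the estimates.
- *Removing selection would let the model isolate carry-over.* The sequences are ABAB and BABA, so a preceding conventional needle means that the current needle is the IQ-Tip. That term cannot separate carry-over from the current needle under any fitting method.

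**Conclusion.** The point holds in a limited form. Running both selection routines on the same 150 to 225 LPs does not verify the robustness of predictors or odds ratios. About 38 to 56 events are available at the 25% planning mean, or 28 to 56 across the article's own pooled rates. Estimates kept by a significance criterion in data of this size tend to be overstated: a true 2.0 appears as roughly 2.3 to 3.1 when kept, depending on rows and threshold. The same would happen if only significant full-model terms were highlighted. Separately, ordinary logistic regression ignores the correlation among up to three LPs per patient, by an amount that cannot be sized here.

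The event count assumes a total of exactly 300, which is a minimum, so it could be higher. The inflation figures rest on assumed prevalences, true effects and thresholds, none of which the article gives, and the simulation behind Step 3 treats rows as independent. The matter is minor: it concerns the credibility of an exploratory table and leaves the primary comparison as it is.

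**What to change.** Make the full prespecified model the only reported result, and show every odds ratio with its 95% confidence interval whatever its p-value. Fit it with patient-clustered standard errors, for example GEE with an independence working correlation, which is the safer choice because the preceding TLP is itself a predictor. Delete the sentence on verification by backward and forward regression. If a stability check is wanted, replace it with bootstrap stability (resampling patients) or penalised estimation. State whether the interval enters as one term or two.

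The cost is a change of wording. No data, visits or sample size are affected. Some confidence intervals may be slightly wider.

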## Discussion

In Finland, about 50 new pediatric patients with ALL are diagnosed every year, and they all are potentially eligible for the present study. Based on our previous experience [19], these young patients and their parents are interested in participating in clinical studies like the present one. Since this study will be conducted in five university hospitals responsible for the treatment of all childhood cancer patients in Finland, the present study sample will be representative of this patient population. Further, the study LP procedures will be conducted within the routine clinical workflow of pediatric hemato-oncology departments, which enhances the pragmatic value of the study within the actual clinical context. Finally, all the study procedures and data collection methods planned to be used in the present study have already been tried out and found feasible for the purpose in our previous single-arm study [19]. Therefore, the overall risk of failure of the present study is deemed negligible.

Being able to perform an LP procedure is one of the fundamental practical skills of every physician. The LP procedures in the study arm B will be performed with conventional Quincke-type spinal needles, which is congruent with established clinical practice. The procedures in the study arm A, in turn, will be performed with the IQ-Tip system, which presents a novel option designed comparable to the standard LP procedure, the added CSF detection functionality and need for an additional cable and analyzer excluded. In addition to two clinical feasibility studies comprising 69 adult and 40 neonatal and infant LP procedures [25, 26], the system has been used in 152 intrathecal therapy procedures of children and adolescents with ALL [19]. According to the SUS-based usability evaluation, the users in the latter study found the system easy to learn and intuitive to use but some expressed a few concerns about the cable and the reliability of CSF detection alarms. The mean SUS score was 75, which is quite satisfactory, for example, in terms of SUS-based results of graphical user interfaces (mean score 76) or cell phones (mean score 66) [28], or a virtual reality-based biopsy simulator (mean score 75) [35]. Further, the present rating was based on the opinions of 20 different physicians representing a broad range of previous experience in performing LP procedures, from less than 10 to hundreds of procedures. All the above issues corroborate the clinical usability of the system and imply a successful method adoption in the present study as well.

Notwithstanding the present study is a non-inferiority trial by design, we expect that the use of the IQ-Tip system will result in a lower incidence of TLP compared with the conventional spinal needle. This expectation rests on the observed incidences of TLP in our previous clinical study [19] and reference data [14]. The first puncture success rate of the IQ-Tip system was 80%, and when the procedure succeeded at the first attempt, the incidence of TLP was about 11% [19]. If this can be reproduced in the present study, one can at least speculate on that the smaller proportion of traumatic procedures could translate into patients’ better event-free survival in the long term. According to the literature [4, 5, 7, 10, 11], blasts can reside in over 50% of CSF samples drawn from traumatic LP procedures at the beginning of the patients’ intrathecal therapy. Blasts in CSF are known to reduce the probability of event-free survival within the timeframe from 5 to 10 years [4, 5, 7, 10, 11]. This increased risk may concern two to four out of 10 patients with ALL, whose initial LP procedures were traumatic and contaminated by blasts. Based on the electronic health record data from two Finnish university hospitals [14], about 20% of diagnostic LP procedures were traumatic as per the threshold of 10 erythrocytes/μL. This means that approximately 10% of CSF samples of the diagnostic procedures may contain blasts and thus indicate a poorer long-term prognosis. Reflecting the above numbers to 50 new annual cases in Finland, this would mean one to two patients every year who will have a poorer long-term recovery since blasts have contaminated their CSF because of TLP. Speculatively, if we were able to halve the incidence of TLP in pediatric patients with ALL, at least one additional child with ALL (2% of the target population) would survive without CSF-related malignant events in Finland. Considering the new cases at the European level [2], this improvement would mean more than 100 new successfully recovered children. Since the current patient’s treatment protocol of ALL is based on personalized risk assessment [3], avoiding an initial TLP may alleviate the evaluation of personal risk leading to a less intense chemotherapy protocol, which again would reduce the patients’ total burden from intrathecal and systemic chemotherapy [10, 36].

Early stylet removal technique, proposed already in the late 80 s [37], has been associated with a higher success rate of LP procedures [38–40], but not necessarily [41]. A recent large randomized controlled trial of neonates showed that the timing of the stylet removal had no discernible effect on the success of LP procedure [42]. Compared with the traditional “blind” puncture, the fundamental idea of the early stylet removal technique is to verify the correct anatomic location by observing CSF flow immediately after the needle tip is inside the subarachnoid space. This way overshooting the needle and piercing the highly vascularized plexus of the ventral epidural space may be avoided and consequent hemorrhage into the subarachnoid space prevented. However, depending on the CSF pressure, length, and lumen size of the spinal needle, the CSF flow may take a few seconds through the needle cannula before being detected, and the provider may continue to advance the needle. This may particularly happen if the haptic feedback from the perforated dura is somehow perturbed, e.g., because of accumulated scar tissue caused by several previous LP procedures of the patient or different haptic feedback from the needle tip without a stylet. Whereas employing the continuous bioimpedance measurement at the needle tip, the IQ-Tip system can detect CSF in real-time. Instead of waiting for the first drop of CSF, the system immediately gives an alarm when the needle tip has reached the correct location for drawing the CSF sample or injecting the intrathecal therapy. To prevent false-positive CSF detections, the provider needs to be careful that the needle tip does not get out from the subarachnoid space when removing the stylet from the needle. Naturally, the same prudence needs to be exercised when the LP procedure is performed with a conventional spinal needle.

The present study is a part of the mandatory post-market clinical follow-up of the novel IQ-Tip system within the scope of its intended use. As per the regulation MDR (EU 2017/745), manufactures of medical devices are required to conduct clinical evaluation of their products. For high-risk medical devices, including spinal needles because of their contact with the central nervous system, the requirements are stringent and rigorous clinical investigations are required. Serious adverse events or unforeseen risks that would be probably linked to the use of the IQ-Tip system or the device per se are not anticipated, but their existence cannot be ruled out. Therefore, the more accumulated clinical data gathered with the given device without serious adverse events, the higher the certainty of its overall clinical safety. Besides serving the regulatory purpose, the present trial will provide sound scientific evidence on the clinical benefit, performance, and safety of the IQ-Tip system compared with the standard clinical practice of using conventional spinal needles in the LP procedures of pediatric hemato-oncology patients.

### Trial status

The first study procedure was performed on 11 May 2023. The protocol version is 1.1 (date 13 April 2022).

## Data Availability

The trial dataset generated and/or analyzed during the current study will not be publicly available due to ethical and data privacy issues in health care but will be partly available from the corresponding author or sponsor upon reasonable request. The CRF templates for both study arms may be delivered upon reasonable request. The principal investigator and sponsor representatives will have access to the final pseudonymized trial dataset, and they and the local principal investigators (i.e., the research group) will discuss and agree on the authorship, relevant avenues of reporting, and dissemination of the trial results to different target groups. The focus will be on high-quality open-access scientific publications. Professional writers will not be used.
